#### Blinding

Participants are blinded to their assignment group and to the existence of a placebo group. The placebo app is also named Stop-tabac - it looks almost the same as the complete app but with fewer features. Thus, control participants may not easily realize that they receive a placebo app. Participants will be informed about the placebo-controlled study design after the end of the study only, and they will be given access to the full version of the app at this point. It is ethical to avoid informing participants of the placebo procedure, because informing them could jeopardize the blinding and stimulate them to use other smartphone apps, thus contaminating the control group. It is ethical to use a placebo-controlled study design because we do not know whether the Stop-tabac app or any other similar app is effective for smoking cessation.

For baseline and follow-up surveys, online data collection is fully automatic, and thus, there is no bias in online assessments. People who do not respond to the online survey receive the follow-up questionnaires by postal mail, and those who do not respond to the postal communication answer the questionnaire over the phone. Assistants who send text or WhatsApp reminder messages and who collect questionnaires by post and over the phone are blinded to the group assignment of participants, to avoid bias. The data analyst is blinded too. The only person with access to the code linking names and group membership is a computer expert who works under the supervision of the first author ([name]), and the data will be unblinded only after the main analysis is finished. There will be no unblinding during the trial.

#### Test of procedures

To ensure that the trial runs smoothly, all procedures (data collection, reminders, supervision of participants) were tested in 15 people (7–8 in each study group) before the study started. In this test, procedures were tested until the 1-month follow-up survey only (i.e. not at 6 months).

### (Fig. 2) Intervention and control group procedures

#### Procedures for both study groups

Registration in the study is accessible only to participants who download the app; this ensures that all participants install the app on their phone. We do not ask participants to avoid using other smoking cessation treatments during the study because this would be unethical.

**Fig. 2 Fig2:**
[figure not shown]
Schedule of enrolment, interventions, and assessments. NRT, nicotine replacement therapy

#### Intervention: the Stop-tabac application for smartphones

The Stop-tabac app is available for iOS (Apple) and for Android, and it was used by 24,000 people every month before we started this study. We used two strategies to ensure that prior users of the app did not register in the trial, and to enroll only new, naïve users. First, we deactivated new downloads one month before we started the study. Because users usually use the app for only a few days or weeks (very few use it for more than 4 weeks), this strategy gradually purged the stock of current users before the study started. Second, in the baseline survey, we asked participants whether they had already used the Stop-Tabac app and we excluded those who had. These two strategies ensure that the study results are not influenced by participation in the control group of prior users of the app.

This smartphone app, in French, is a stand-alone intervention intended at motivating and helping smokers quit smoking. It has been developed since 2012 by experts in addiction and continuously improved thereafter, taking into account the suggestions made by users in face-to-face tests and in online satisfaction surveys. The app is based on behavior change and addiction theories [37–39], on guidelines and literature reviews on treatments for tobacco dependence [11, 27], and on the applicants’ research [40] and experience with smokers. The app includes:
Brief texts on tobacco dependence, tobacco withdrawal symptoms, tobacco dependence treatments, relapse situations, mood management, risks of smoking and benefits of quitting, e-cigarettes, and heated tobacco products.Calculators (number of cigarettes not smoked, money saved since quitting, additional days of life expectancy gained since quitting).Immediate feedback when participants experience challenging situations (e.g. relapse situations, craving episodes).A quiz (42 questions), which allows the transmission of knowledge in a playful way.A link that automatically dials the phone number of the national quit-lines in France or Switzerland.The “Coach”, an automatic system that produces individually tailored feedback messages and sends periodic reminders (push notifications within the app). Each participant receives individually tailored advice and follow-up messages based on their target quit date, level of tobacco dependence, perceived advantages and drawbacks of smoking, and motivation to quit. The duration of this automated intervention is 6 months. Participants can disable the push notifications.A discussion forum, “The Tribe”, permanently (24 h a day/7 days a week/365 days a year) moderated by a psychologist helped by volunteers under her supervision. An influential guideline identified social support as an important and effective component of smoking cessation interventions [27]. The “Tribe” is quite active and is very appreciated by users.A module on nicotine replacement therapy (NRT) that includes fact sheets (NRT utilization, benefits and side effects, where and how users can obtain NRT); frequently asked questions (FAQ); and a series of brief individually tailored feedback messages, based on users’ responses to questions on current NRT use, knowledge about NRT, intention to use NRT, craving and withdrawal symptoms. If users report withdrawal symptoms and if they have quit smoking for < 3 months, they receive automated messages telling them to use NRT. These messages insist on the importance of using a sufficient dose of nicotine and not interrupting the treatment prematurely.A module on electronic cigarettes that includes a series of brief individually tailored feedback messages, based on users’ responses to questions on current vaping, intention to use e-cigarettes, opinions about the effects of vaping on smoking cessation and nicotine withdrawal symptoms, perceived side-effects, and perceived addictiveness of e-cigarettes.

The Stop-tabac.ch application belongs to the University of Geneva, it is available at no charge on the app stores, and the investigators of this study and the authors of the app have no financial interest in this app, and no conflict of interest with the pharmaceutical, tobacco or e-cigarette industries. The development and maintenance of the Stop-tabac app are supported by the Swiss Tobacco Prevention Fund (at the Swiss Ministry of Health), and the app does not receive support from the pharmaceutical, tobacco, or e-cigarette industries. During the study, the app is only available to study participants.

The conditions of use of the app in the trial are similar to the conditions of use outside the trial. In particular, the frequency of use of the app is determined by the users themselves, and we do not use any prompts or reminders to trigger utilization of the app (no SMS or e-mail), apart from the notifications normally sent within the app itself.

#### Control group procedures

The placebo app includes a few features that are liked by users (brief information pages, calculators of money saved, cigarettes not smoked, and days of life expectancy gained). We do not think that this content is sufficient to produce an impact, but it should prevent the potential problem that the placebo app is so basic and unsatisfactory that control participants access other support more frequently than intervention participants, which may bias the results in the direction of null findings. After randomization, we only contact participants in both study groups for the three follow-up surveys.

#### Study software and data protection

A special software was set up to manage the study, enroll participants, and conduct baseline and follow-up surveys. Participants’ information is kept confidential and accessible only to the members of the research team (the project leaders, a computer expert and two research assistants). The dataset for analysis will be anonymized. The only person who can access the code linking participants’ names and their responses to questionnaires is a computer expert under the supervision of the first author.

#### Data to be collected

The primary outcome is self-reported smoking abstinence after 6 months (no puff of tobacco in the past 4 weeks). This is the criterion recommended by the American Food and Drug Administration (FDA) to assess outcome in smoking cessation studies [41]. We also assess outcome using the “Russell Standard”, a recently suggested standard for smoking cessation trials: continuous 6-month (at 6 months) or 1-month (at 1 month) abstinence allowing for smoking ≤ 5 cigarettes after the target quit date, but no cigarette in the past 7 days [36].

#### Baseline data

The baseline online questionnaire, in French, is administered through a mobile-friendly website, accessible via any platform: smartphone, tablet, or computer. Baseline variables include smoking behavior, tobacco dependence, current use of nicotine medications, e-cigarettes, and heated tobacco (Iqos, Glo, Ploom, or other brand), age and sex, a brief (two items) screening test for depression [42], postal address, telephone number, and e-mail address.

#### Follow up after 1 week, 1 month and 6 months

The date for follow-up surveys is tied to the target quit date set at baseline. Follow-up data are collected online, via a questionnaire accessible on all platforms. Participants receive an invitation by e-mail to answer the follow-up questionnaires 1 week, 1 month and 6 months after their target quit date. After reminders via e-mail (7 days: four reminders; 1 month: six reminders; 6 months: eight reminders), this online data collection is fully automatic. The next steps only involve a human intervention: assistants send non-responders three reminders via text messages (or WhatsApp) on their cellphones, then non-respondents receive the follow-up questionnaire by post, and those who do not respond to the postal questionnaire are contacted by phone [43]. Follow-up questionnaires are brief and focused, in order to maximize participation.

#### No biochemical verification of smoking cessation

The Society for Research on Nicotine and Tobacco (SRNT) guidelines for assessing outcome in smoking cessation studies do not recommend biochemical verification when there is no close contact or interaction between participants and the study team [44]. Although the absence of biochemical verification may result in some under-reporting of smoking, this should not differ between the intervention and control groups, so this should not impact the test of effectiveness.

#### Potential bias

Participants consist of volunteers and may not be representative of all smokers. We will compare our sample to representative samples of smokers in Switzerland and France. There are no restrictions to obtaining smoking cessation support outside the study. We ask participants whether they used NRT, e-cigarettes, heated tobacco, or smoking cessation apps during the study, and will use this information in our analysis and interpretation of the results.

There is a risk that participants in the more engaging “complete” app (with push notifications) will be more burdened and delete the app or disable the app notifications, but the current content and frequency of reminders have been considered acceptable by app users over the years.

All answers are given via drop-down menus or radio buttons (except names and addresses), and thus only valid answers are recorded. At baseline, participants are required to answer all questions (an incomplete form cannot be sent) and thus there are no missing data. At follow up, answers to the questions on smoking status (any smoking in the past 7 days, 4 weeks, and 6 months) are required, but participants can send an incomplete form as long as they answer these questions. An assistant will enter the data for questionnaires on paper (collected by post or over the phone) by single data entry.

#### Sample size calculation

Based on the literature on Internet-based text messaging and smartphone interventions [12, 45], and on our own prior studies of Internet-based interventions [40, 46], we expect quit rates of 12.5% in the complete app group and 10% in the placebo group after 6 months (odds ratio = 1.28). The difference of 2.5 percentage points may appear to be small, but it is about half of the effect of nicotine replacement therapy combined with medical counseling (6% above placebo) [26], or the effect of bupropion (5% above placebo) [47], or the effect of intensive smoking cessation counseling by physicians (5% above usual care) [48]. Thus, an effect of 2.5 percentage points is actually quite large, and it would not be reasonable to expect a much larger effect. An effect of 2.5 percentage points applied to tens of thousands of users translates into a substantial impact at population level. A total of 5200 smokers (2 × 2600) will enable us to detect this effect with power of 80% and a confidence level of 95%.

#### Intention to treat, missing data

For the primary outcome, participants will be evaluated in an intention-to-treat analysis, with the baseline number of participants as the denominator. Participants absent at follow-up will be counted as smokers, except those who are dead. We will conduct sensitivity analyses with different assumptions for missing data. For each follow-up questionnaire, non-responders will be counted as smokers for this specific questionnaire. A participant who is missing at the 1-month follow up but then returns as a non-smoker for the 6-month follow up will be counted as smoker for the 1-month follow up only.

#### Discontinuation criteria, protocol modifications

Participants can withdraw from the study at any point, without having to justify their decision. Participants need to inform the researchers to be classified as withdrawing. Participants who withdraw from the study are not given access to the full app, but the full app will be freely accessible to all after the end of data collection.

There is no plan to amend or modify the study protocol. If the protocol must nevertheless be modified, we will amend the ISRCTN record, and we will mention in all published papers that the protocol was modified during the study, and how it was modified. Assistants who contact non-respondents worked at home during the lockdown during the epidemic in Spring 2020, performing their usual tasks.

#### Risks to participants

There is no risk associated with the behavioral program and the data collection procedure. There is a risk that data may be accessed by hackers. We make every effort to minimize this risk by using appropriate security measures.

#### Dissemination policy

Results will be published in peer-reviewed journals and presented at conferences; there is no publication restriction. Both co-investigators ([name] and YK) will be co-authors; if there are any other contributors, authorship will be granted according to the usual rules. We do not intend to use professional writers. After publication of the study results, participant-level data and the statistical code will be made publicly accessible in an anonymous format.

#### Confidentiality

The data are stored on computers at the University of Geneva and at an external provider, with high levels of security. The dataset for analysis will be anonymized. The only person who can access the code linking participants’ names and their responses to questionnaires is a computer expert under the supervision of the first author. Data will be anonymized before they are made publicly available on a repository.

### Statistical analyses and data management

The main analysis will be a comparison of the proportions of abstinent smokers (as defined above) after 6 months in the intervention and control groups. We will use the chi-square test and odds ratios with 95% confidence intervals to compare proportions. We will also conduct subgroup analyses and will use multivariate models to test whether the outcome is associated with participants’ characteristics and with smoking cessation tools obtained outside the study. We will assess whether the outcome is associated with the frequency of utilization of the app (from usage data automatically collected by the app). The study is conducted and results will be presented in conformity with the Consolidated Standards of Reporting Trials (CONSORT) guidelines [49] and CONSORT E-Health checklist [50]. Creating a data monitoring committee was not deemed necessary because the data are collected mostly automatically, and because only valid answers can be entered in the online forms via drop-down menus or radio buttons, thus no major quality issues arise with this data set. The data will be accessible to the two co-investigators ([name] and YK), and after publication of the study results, participant-level data and the statistical code will be made publicly accessible in an anonymous format.

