##### Secondary outcomes

Secondary outcomes are:
Smoking cessation: proportion of participants who report they have not smoked even a puff of tobacco in the previous 7 days, assessed at each follow-up.Smoking cessation as defined in the Russell Standard [36]: proportion of participants at the 6-month follow up who report they smoked ≤5 cigarettes in the past 6 months but did not smoke even a puff of tobacco in the past 7 days, and proportion of participants at the 4-week follow up who report they smoked ≤ 5 cigarettes in the past 4 weeks but did not smoke even a puff of tobacco in the past 7 days.Abstinence from both smoking and vaping: the proportion of participants who report they did not smoke any tobacco or use nicotine-containing e-cigarettes or heated tobacco products after their target quit date, assessed at each follow up.Nicotine use: the proportion of participants who used nicotine therapy, nicotine-containing e-cigarettes or heated tobacco after their target quit date, assessed at each follow up.Perceived usefulness of the app: the question reads: “Did the *Stop-Tabac* app for mobile phones help you quit smoking?”, and is answered on a Likert-type scale with 6 response options ranging from “Yes, enormously” to “On the contrary, it made me smoke or start smoking again”, assessed at each follow up.App use: the proportion of participants who report using any smoking cessation app after their target quit date, assessed at each follow up.

Among those who smoke at follow up:
Intention to quit smoking: the proportion of participants who answer each of the response options to the question: “Do you intend to quit smoking? (response options: I have firmly decided to quit/I consider quitting/No), assessed at each follow up.Quit attempts: the proportion of participants who report they seriously tried to quit smoking after their target quit date (response options: yes/no), assessed at each follow up.Amount smoked: mean number of cigarettes smoked per day, and change since baseline in cigarettes per day (mean change score), assessed at each follow up.

Secondary outcomes from data collected automatically by the app:
Duration of app use (mean number of days between the first and last use of the app) and frequency of app utilization (mean number of times the app was opened), recorded automatically at individual level, assessed at 6-month follow up only.

Inclusion criteria:

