#### Randomization

Participants are randomized only after we receive the baseline survey and the consent form, and after we verify eligibility. Eligibility is assessed automatically by computer algorithms. We perform an automated check of e-mail addresses, names, age, and sex, to avoid double registration of participants. Once a candidate is declared eligible, randomization is automatically performed by a computer using a list of random numbers, with a 1:1 ratio and using simple randomization, with no strata or block. After randomization, participants receive a personal code number in an e-mail message, they insert this code number manually in the app on their smartphone, and at this point they can access either the complete Stop-tabac app or to the placebo app. This procedure ensures that participants register only once, that all of them open the app, and that they have access to their intended intervention only. Participants who do not manually enter their personal code in the app do not have access to any version of the app and are excluded after randomization. Access to the app is restricted to study participants during the study; non-participants cannot access or download the app.

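### The primary comparison is a valid but unadjusted chi-square test, although complete baseline predictors are collected; pre-specified baseline adjustment would recover a small amount of precision

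*Protocol article*

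**What the plan says.** - **Main analysis** (Statistical analyses and data management): abstinence proportions at 6 months are compared between arms. "We will use the chi-square test and odds ratios with 95% confidence intervals to compare proportions". No covariate is named. Multivariate models are also planned, but to see whether the outcome is associated with participants' characteristics and with cessation aids obtained outside the study. They are not described as giving an adjusted treatment effect.
- **Baseline data** (Baseline data; Potential bias): smoking behaviour, dependence, use of nicotine medications, e-cigarettes and heated tobacco, age, sex and a two-item depression screen. On completeness: "At baseline, participants are required to answer all questions (an incomplete form cannot be sent) and thus there are no missing data".
- **Allocation** (Randomization): 1:1, "using simple randomization, with no strata or block".
- **Sample size** (Sample size calculation): "we expect quit rates of 12.5% in the complete app group and 10% in the placebo group after 6 months", also given as "odds ratio = 1.28". The total is 5200, or 2600 per arm, which "will enable us to detect this effect with power of 80% and a confidence level of 95" percent.
- **Cigarettes per day** (Secondary outcomes): two summaries are listed, the mean at follow-up and the "change since baseline in cigarettes per day (mean change score"), both only among those smoking at follow-up. No test or model is given.

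**The concern.** The protocol's own secondary objectives name dependence, sex, age, smoking history and depression as possible influences on outcome. These are observed for everyone before randomization, yet the main test does not use them. Because allocation is unstratified, the analysis is the only place where this information can be used.

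Adjusting for baseline predictors keeps the comparison valid and usually narrows the confidence interval. The Sample size calculation section argues that a much larger effect than 2.5 percentage points is not a reasonable expectation, so precision that needs no extra data is worth having. That section argues mainly in percentage points, while the only effect measure named for the analysis is the odds ratio. A risk difference with its interval would report the quantity argued from.

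The planned multivariate models do not fill this gap. Cessation aids used during the study are measured after randomization, and the app has a module meant to increase nicotine replacement use. A model that adjusts for such aids could remove part of the app's effect.

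**Working it through.** **1. The plan's own figure.** Inputs from Sample size calculation: p1 = 0.125, p0 = 0.10, difference d = 0.025, 95% confidence read as two-sided alpha 0.05, power 80%.

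- Odds ratio: (0.125/0.875)/(0.10/0.90) = 1.286, against 1.28 stated.
- Mean risk 0.1125. Pooled term √(2 × 0.1125 × 0.8875) = 0.4469. Unpooled term √(0.125 × 0.875 + 0.10 × 0.90) = 0.4465.
- n per arm = (1.96 × 0.4469 + 0.8416 × 0.4465)² / 0.025² = 2507, total 5014. With continuity correction it is 2586, total 5172, close to the stated 5200.
- Power at 2600 per arm: Φ[(0.025 × √2600 − 1.96 × 0.4469)/0.4465] = Φ(0.893) = 81.4%.
- Standard error of the risk difference: 0.4465/√2600 = 0.00876, a 95% half-width of 1.72 percentage points.

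The stated size reproduces.

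**2. Effect of adjustment on the primary outcome.** If baseline variables explain a share R² of the outcome variance, the standard error is multiplied by √(1 − R²), and the effective size per arm is 2600/(1 − R²). The documents give no R², so the range is assumed.

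| Assumed R² | Effective n per arm | Power | Half-width (points) | Total N for 80% power |
|---|---|---|---|---|
| 0 | 2600 | 81.4% | 1.72 | 5014 |
| 0.01 | 2626 | 81.8% | 1.71 | 4964 |
| 0.02 | 2653 | 82.2% | 1.70 | 4914 |
| 0.05 | 2737 | 83.3% | 1.67 | 4764 |
| 0.10 | 2889 | 85.3% | 1.63 | 4514 |

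**3. Check by simulation.** 3000 trials per setting, 2600 per arm, marginal risks 10% and 12.5%, one normally distributed baseline predictor:

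| AUC | R² | Chi-square power | Adjusted logistic power | Conditional odds ratio |
|---|---|---|---|---|
| 0.58 | 0.008 | 81.8% | 81.8% | 1.289 |
| 0.64 | 0.023 | 80.5% | 81.3% | 1.294 |
| 0.69 | 0.046 | 81.4% | 82.9% | 1.303 |
| 0.75 | 0.092 | 81.9% | 85.9% | 1.321 |

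Each power carries a simulation error of about √(0.81 × 0.19/3000) = 0.7 points. The pattern agrees with step 2: nothing visible for weak predictors, and about 4 points at an AUC of 0.75. The conditional odds ratio moves away from the marginal 1.286, so the plan must say which one is meant.

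**4. Chance imbalance.** With 2600 per arm, the standardized difference of a baseline variable has SD √(2/2600) = 0.028, so 95% of differences lie within about ±0.054.

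**5. Cigarettes per day.** Let r be the baseline to follow-up correlation, with equal SDs at both times (both assumed). In units of the outcome variance, the follow-up mean has factor 1, the change score 2(1 − r), and the baseline-adjusted comparison 1 − r². The ratio of adjusted to change score is (1 − r²)/[2(1 − r)] = (1 + r)/2: 0.65 at r = 0.3, 0.75 at 0.5, 0.85 at 0.7 and 0.90 at 0.8.

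**The case against.** The strongest case is that nothing here is wrong. An unadjusted chi-square test is valid under 1:1 randomization, is the test the trial was sized for, and already has 81.4% power. At R² of 0.05 the half-width shrinks only from 1.72 to 1.67 points, and every R² is assumed. Recruitment had finished by March 2020, the protocol foresees no amendment, and choosing covariates late adds some analytic freedom. All of this stands. It limits the point to a suggestion about efficiency. Blinding of the analyst lessens the worry about late choice, though it does not remove it.

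Four stronger readings are tempting, and the document does not support them:

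- *The primary analysis is flawed or underpowered.* The stated size reproduces, and the test is valid.
- *Unstratified allocation leaves the arms unbalanced.* Randomization balances in expectation, step 4 shows that large differences are unlikely, and the test's error rate already allows for them.
- *Cigarettes per day is analysed only as a raw change score.* The follow-up mean is listed as well, and no model is stated. A baseline-adjusted comparison is compatible with that text, and an analysis plan that is not shown may supply one.
- *The odds ratio contradicts the basis of the sample size.* That section gives the target both as 2.5 points and as an odds ratio, so a missing risk difference is a reporting gap at most.

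**Conclusion.** The point holds as a modest efficiency improvement. The main comparison uses none of the complete baseline information, and no baseline-adjusted treatment effect is named elsewhere in the protocol. The cost on the primary outcome is about 0.4 to 2 power points for assumed R² of 0.01 to 0.05, and about 4 points at 0.10. The larger gain requires baseline variables that predict abstinence with an AUC near 0.75, which the document gives no ground to assume or exclude.

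For cigarettes per day, baseline adjustment would cut variance by 10% to 35% relative to the change score for r from 0.8 to 0.3, given equal SDs. That gain has a limit: the outcome is restricted to those still smoking at follow-up, a group formed after randomization. Adjustment sharpens that comparison but does not make it a fully randomized one.

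**What to change.** Before unblinding:

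1. Pre-specify a logistic model of 6-month abstinence on arm plus named baseline covariates: dependence, smoking behaviour, nicotine-product use, age, sex and depression screen. Exclude anything measured after randomization, in particular cessation aids used during the study.
2. Standardize the model to a marginal risk difference and a marginal odds ratio, each with a 95% confidence interval, so that the estimates match the quantities in the Sample size calculation section.
3. Report this with the unadjusted chi-square result, and state in advance which of the two carries the primary conclusion. The power gain is realized only if the adjusted one does.
4. Compare follow-up cigarettes per day adjusted for the baseline value. State that the comparison covers only those still smoking and is not fully randomized.

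The cost is analysis wording and a few lines of code. No new data are needed, and no participant is lost to missing covariates. The protocol's section on modifications also requires an amended ISRCTN record and a mention in all published papers.

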## Methods/design

### Objectives

The objective is to test whether the Stop-tabac smartphone application (iOS and Android) improves smoking cessation rates in current smokers and helps them maintain abstinence over 6 months, compared with quit rates observed in a control group, and to measure the size of this effect.

Secondary objectives are:
To study whether the outcome is influenced by the characteristics of participants, such as dependence level, demographics (sex and age), smoking history, and depression.To assess whether the app has any effect on motivation to quit, quit attempts, use of NRT, e-cigarettes and heated tobacco products, number of cigarettes smoked per day, and perceived usefulness of the app.

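### Counting absent participants as smokers appears to carry into the models of who quits, where a characteristic that only affects answering can look like a predictor of quitting

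*Protocol article*

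**What the plan says.** All references are to the protocol article.

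- **Intention to treat, missing data.** For the primary outcome the denominator is everyone enrolled at baseline, and "Participants absent at follow-up will be counted as smokers, except those who are dead". The section then applies the same rule questionnaire by questionnaire, without limiting it to the arm comparison. It also promises sensitivity analyses under other missing-data assumptions, which it neither names nor ties to a particular analysis.
- **Statistical analyses and data management.** After the arm comparison, the team "will use multivariate models to test whether the outcome is associated with" participant traits and cessation aids found elsewhere. No separate handling of non-response is given for these models.
- **Objectives.** The first secondary objective is "To study whether the outcome is influenced by the characteristics of participants", with dependence, sex, age, smoking history and depression as examples.
- **Potential bias.** Baseline forms cannot be sent incomplete, so every participant has baseline covariates. At follow-up only the smoking-status items are compulsory. On outside help: "We ask participants whether they used NRT, e-cigarettes, heated tobacco, or smoking cessation apps during the study". The Secondary outcomes section shows that such use is asked about at every follow-up.

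**The concern.** Between randomized arms, absent = smoker is a familiar convention, and randomization balances the tendency to answer at the outset. The characteristics models compare kinds of people: older with younger, depressed with not depressed. Nothing balances the tendency to answer across those groups. Because baseline data are complete, non-responders can stay in the models, all scored as smokers, and the fitted association then mixes who quits with who answers.

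At stake is the first secondary objective. False predictors could be declared and real ones hidden, in a sample of 5200 where modest differences reach significance.

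The outside-aids model has a further difficulty. Use up to 6 months is known only from follow-up answers, so a 6-month non-responder scored as a smoker has an incomplete covariate or none.

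**Working it through.** **The plan's own figure.** Inputs (Sample size calculation): "we expect quit rates of 12.5% in the complete app group and 10% in the placebo group after 6 months"; 80% power; 95% confidence, taken as two-sided 5%.
- n per arm = [1.96·√(2·0.1125·0.8875) + 0.8416·√(0.125·0.875 + 0.10·0.90)]² / 0.025² = 2507. With continuity correction it is 2586, or 5172 in total, against the stated 5200.
- Power at 2600 per arm is 81.4%.
- Odds ratio = (0.125/0.875)/(0.10/0.90) = 1.286 (stated 1.28).

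The sample size reproduces, and nothing below changes it.

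**Size of the false association.** Scored quit rate = true quit rate Q × share of quitters who answer. The documents give no response rates, so every rate here is an assumption. Take a characteristic that splits the sample 2600/2600, is unrelated to quitting, and has Q = 16% in both halves. In one half 65% of quitters answer, so the scored rate is 0.16 × 0.65 = 10.4%.

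| Quitters answering, other half | Scored rate | False OR | Rejection, two-sided 5% test | Same, Q = 12% to 20% |
|---|---|---|---|---|
| 70% | 11.2% | 1.09 | 15% | 12–18% |
| 75% | 12.0% | 1.18 | 45% | 34–55% |
| 80% | 12.8% | 1.27 | 77% | 63–87% |

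Example: (0.128/0.872)/(0.104/0.896) = 1.265. The rejection figures are for a simple comparison of two proportions; an adjusted model will differ somewhat.

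**Would a missing-at-random analysis be safer?** Let overall response be 80% against 65% and true quitting 16% in both halves. Let non-responders quit at f times the responders' rate. Responders' rate = 0.16/[r + (1−r)f]; scored rate = r × responders' rate. The responders' odds ratio stands in for missing-at-random.

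| f | Responders' rates | OR, responders | Scored rates | OR, absent = smoker |
|---|---|---|---|---|
| 1 | 16.0% v 16.0% | 1.00 | 12.8% v 10.4% | 1.27 |
| 0.5 | 17.8% v 19.4% | 0.90 | 14.2% v 12.6% | 1.15 |
| 0 | 20.0% v 24.6% | 0.77 | 16.0% v 16.0% | 1.00 |

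The truth is 1.00 in every row. The two scorings err in opposite directions and bracket it, provided f lies between 0 and 1 and is the same in both halves. Imputation that uses earlier answers may do better than this stand-in.

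**Treatment effect within levels.** Suppose quitting is 16% v 12.8% by arm and response is equal between arms. At 80% response the scored rates are 12.8% v 10.24% (risk ratio 1.25, OR 1.29). At 60% they are 9.6% v 7.68% (risk ratio 1.25, OR 1.28). Effect-modification results barely move.

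**The case against.** **The carry-over is an inference.** The missing-data section opens with the primary outcome, and the analysis section speaks only of the outcome. A condensed article may leave secondary model details to a fuller document. This stands to the extent that the plan cannot be said to state the carry-over. It does not remove the point: the per-questionnaire rule is unrestricted, and it is the only scoring of non-responders the document defines.

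**Sensitivity analyses are already planned.** They might cover these models. But their assumptions are unnamed and they are not linked to this objective, so they give no rule for what may be called a predictor.

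**The size is assumed.** This stands. Follow-up is intensive (at 6 months eight e-mail reminders, then text messages, post and telephone), and the bias vanishes if no non-responder has quit or if quitters' response is even across the characteristic.

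**The alternative is no better.** This also stands, as the second table shows, and it is why simply replacing one scoring with the other is not recommended.

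**Outside aids.** A reader might infer that the score cannot work at all here, or that it builds in a large false association. Coding non-responders as non-users, with 40% use among responders, 11% scored abstinent and no true link, would give an OR of 1.5, 2.1 or 3.1 at 80%, 65% or 50% response. The documents do not support that reading. They never propose such coding, and a participant absent at 6 months may have reported use at 1 week or 1 month. What remains is that use up to 6 months is unknown for 6-month non-responders.

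**Conclusion.** The point holds in a limited form. On the natural reading, the absent = smoker score enters the models of participant characteristics, where response is not balanced by design. A characteristic tied only to answering can then appear to predict quitting. Under assumed response of 65% against 80% among quitters and 16% true quitting, the false odds ratio is about 1.27, close to the 1.28 the trial is sized to detect. With a 5-point gap it is about 1.09. It is 1.00 if no non-responder has quit or if quitters' response does not vary with the characteristic.

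Two stronger conclusions should not be drawn. First, nothing here undermines the comparison between arms or the sample size, and effect-modification results are largely unaffected when response is similar between arms. Second, missing-at-random is not shown to be the right primary scoring: it is biased the other way when non-responders are mostly smokers, and the documents do not show which assumption is closer. Neither scoring should stand alone.

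**What to change.** In the missing-data and statistical analysis sections, add that:

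1. The characteristics models are fitted twice: once with absent = smoker, and once with multiple imputation of 6-month abstinence (from arm, baseline data and the 1-week and 1-month answers) or with responders weighted by the inverse probability of response.
2. Six-month response is tabulated by each characteristic.
3. A characteristic is called a predictor of quitting only if the association holds under both.
4. The outside-aids model is fitted in 6-month responders, and missing use is not coded as non-use.

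This takes a few sentences and a little more analysis, with no new data and no change to the primary analysis. The price is that fewer characteristics will be declared predictors. Agreement under both scorings is a safeguard rather than a guarantee, since quitting among non-responders may itself differ by characteristic.
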